### Specific aims

*Aim 1 (Primary):* To evaluate the clinical effectiveness of a stepped-care intervention for ED patients with panic-related anxiety compared to screening alone.

*Outcomes under Aim 1:* The primary outcome under Aim 1 will be clinician-rated severity of panic symptoms, measured using the Panic Disorder Severity Scale (PDSS) [30] and the Clinical Global Impression Scale (CGI) [31]. Panic disorder will be diagnosed using the Structured Clinical Interview for DSM-5 (SCID) [32].

*Aim 2:* To evaluate the patient-centred effectiveness of a stepped-care intervention for ED patients with panic-related anxiety compared to screening alone.

*Outcomes under Aim 2:* We will examine health-related quality of life using the 12-item Short Form Health Survey (SF-12) [33], and the EuroQoL–5 Dimension (EQ-5D) [34]. We will assess psychiatric comorbidity using the Psychiatric Diagnostic Screening Questionnaire (PDSQ) [35], and healthcare utilization for panic-related symptoms (ED visits and hospital admissions) based on electronic medical record data in the 12 months following the intervention.

*Aim 3:* To evaluate the incremental cost-effectiveness of a stepped-care intervention for ED patients with panic-related anxiety compared to screening alone, from the health system perspective.

*Outcomes under Aim 3:* We will calculate the incremental cost-effectiveness ratio (ICER) of stepped-care intervention relative to screening alone, at 12 months from baseline. Direct healthcare costs will be calculated from electronic billing records and the effectiveness of the intervention will be assessed based on the conversion of SF-12 form to a quality of life weight using the Short Form Health Survey 6D (SF-6D) algorithm [36].

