*Aim 3: To assess the cost-effectiveness of stepped-care* versus *screening alone from the health system perspective:* We will estimate the ICER for the STEP arm participants relative to the SCREEN arm participants at 12 months from baseline. The ICER is calculated as the difference between the costs of the two strategies divided by the difference in their effectiveness. Costs from the health system perspective will be the difference in average costs between those in the STEP and SCREEN arms, based on hospital billing data. The difference in effectiveness will be based on the quality of life weights generated by applying the SF-6D algorithm to scores from the SF-12 survey. The STEP intervention will be considered dominant over SCREEN if it incurs less costs and generates higher quality-adjusted life years (QALYs). STEP will be considered cost effective relative to SCREEN if the ICER is below the cost-effectiveness threshold. We will adopt the National Institute for Health and Care Excellence’s cost-effectiveness threshold of £20,000–30,000 per QALY gained, which roughly translates into $63,313 SGD per QALY gained [51].

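### As written, the Aim 3 rule that STEP is cost effective when the ICER is below the threshold reverses the verdict whenever STEP loses QALYs

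*Protocol article*

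**What the plan says.** The rule stands in the protocol article, Data analysis, under Aim 3. The ratio is defined first: "The ICER is calculated as the difference between the costs of the two strategies divided by the difference in their effectiveness". Effectiveness is measured in SF-6D weights: "The difference in effectiveness will be based on the quality of life weights generated by applying the SF-6D algorithm to scores from the SF-12 survey". Specific aims sets the horizon, with the ICER taken "relative to screening alone, at 12 months from baseline".

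Two verdicts follow. STEP is called dominant if it is cheaper and yields more QALYs. Otherwise, "STEP will be considered cost effective relative to SCREEN if the ICER is below the cost-effectiveness threshold". Nothing is said about STEP being costlier with fewer QALYs, or cheaper with fewer QALYs.

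The threshold is a "cost-effectiveness threshold of £20,000–30,000 per QALY gained", "which roughly translates into $63,313 SGD per QALY gained". The article cites a reference for this but states no exchange rate, no date and no choice of point within the range.

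**The concern.** A ratio of two differences loses the information about which arm is better. A negative ICER can mean that STEP is cheaper and better, or that it is costlier and worse. A positive ICER can mean paying for a gain, or saving money at the price of a loss. A rule that looks only at whether the ratio is below a positive threshold cannot tell these apart. The article separates out one negative-ICER case (dominant) but leaves its mirror image (dominated) to the general rule, which passes it.

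Economic effectiveness is one of three stated aims, and this sentence decides its conclusion. If the QALY estimate came out negative, the pre-specified criterion could support a claim of cost-effectiveness for an arm that is worse and more expensive.

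The threshold adds a smaller uncertainty. A range has been turned into one number without saying which point of the range it stands for, so the reader cannot tell how demanding the test is.

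**Working it through.** **Inputs.** From Data analysis, Aim 3: the ICER definition, the decision rule, the range £20,000–30,000 and the figure SGD 63,313. From Sample size: 80 participants per arm after attrition. Assumed, because the article gives no such figures: a true QALY gain of 0.02 or 0, and a between-person QALY SD of 0.10–0.15. The cost and QALY pairs below are illustrations.

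**Step 1: algebra of the rule.** Let dC and dQ be the cost and QALY differences (STEP minus SCREEN), and let L > 0 be the threshold. Net monetary benefit is NMB = L × dQ − dC.

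- If dQ > 0, dC/dQ < L is equivalent to dC < L × dQ, so NMB > 0. The rule is right.
- If dQ < 0, multiplying by dQ flips the inequality: dC/dQ < L is equivalent to dC > L × dQ, so NMB < 0. The rule is reversed.

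**Step 2: examples at L = 63,313 (SGD).**

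| dQ | dC | ICER | Stated rule | NMB |
|---|---|---|---|---|
| +0.02 | +1,000 | 50,000 | cost effective | 1,266 − 1,000 = +266 |
| +0.02 | +2,000 | 100,000 | not | 1,266 − 2,000 = −734 |
| −0.01 | +500 | −50,000 | cost effective | −633 − 500 = −1,133 |
| −0.02 | −200 | 10,000 | cost effective | −1,266 + 200 = −1,066 |
| −0.02 | −2,000 | 100,000 | not | −1,266 + 2,000 = +734 |

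The two rows with a gain are classified correctly and the three with a loss are not. The third row is the dominated case and is wrong at any positive threshold. The last two value a QALY lost the same as a QALY gained.

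A numerical check used 400,000 random pairs, with dQ uniform on ±0.1 and dC uniform on ±10,000. All 199,806 pairs with dQ < 0 were misclassified, and none of the 200,194 with dQ > 0. These counts confirm the algebra. They are not probabilities for this trial.

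**Step 3: how often the QALY estimate could be negative.** The standard error of dQ is SD × √(2/80) = SD × 0.158, and P(dQ estimate < 0) = Φ(−gain/SE).

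- Gain 0.02, SD 0.10: SE 0.0158, Φ(−1.265) = 0.10.
- Gain 0.02, SD 0.15: SE 0.0237, Φ(−0.843) = 0.20.
- Gain 0: 0.50 at any SD.

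A larger true gain would lower these figures.

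**Step 4: the threshold figure.** SGD 63,313 cannot be reproduced, because the article gives no rate. The implied rates are:

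- as £20,000: 63,313/20,000 = 3.17 SGD/GBP
- as £25,000: 63,313/25,000 = 2.53
- as £30,000: 63,313/30,000 = 2.11

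So the figure lies inside the range for any rate between about 2.11 and 3.17, equals the upper bound at 2.11, and exceeds the range below that. The article does not say which applies.

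**The case against.** The best defence of the rule is its context. The threshold is worded per QALY gained, in pounds and again in Singapore dollars, and the preceding sentence on dominance considers the directions of cost and effect separately. A health economist would not call a costlier, less effective arm cost effective. This stands as mitigation: the authors very probably had a QALY gain in mind. But the phrase is the unit of the threshold, not a condition on the rule. A pre-specified criterion should give the right answer as written, and this one does not.

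A second defence is that the full protocol or an analysis plan may hold more detail. That is a good answer to any complaint about missing bootstrap methods, acceptability curves or covariate adjustment, and none is made here. It does not answer a published rule that is wrong for every QALY loss.

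On the threshold, using one working value from a range is legitimate, and the article says the translation is rough. A reader might infer that SGD 63,313 sits at or above the top of the range and is therefore the most lenient reading. The article does not support that, because it depends on an exchange rate that is not given. Nor does anything in it require the lower bound for a claim of cost-effectiveness. What remains is that the rate, the date and the chosen point are unstated.

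**Conclusion.** The point holds for the decision rule. Read literally, it reverses the verdict for every QALY loss, apart from exact ties. It wrongly accepts a dominated STEP and a cheaper STEP that saves too little per QALY lost, and it wrongly rejects a cheaper STEP that saves enough. With a QALY gain it works correctly. The dominated case needs no assumption beyond a positive threshold. The cheaper-but-less-effective cases assume that losses and gains are valued alike.

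Whether the fault would bite depends on the QALY estimate. The 10–20% figure rests on the assumed gain and SD, so a negative estimate is plausible. A reader might go further and call it likely, but that would need little or no true QALY effect, and the article gives no basis for assuming so.

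The threshold point is secondary: one SGD figure of unstated derivation, which matches £30,000 at 2.11 SGD/GBP and £25,000 at 2.53.

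Severity is moderate. Aim 1 is labelled primary, and its outcomes, data collection and analysis are untouched. Only the Aim 3 conclusion is at risk.

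**What to change.** Replace the rule with one of the following:

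- Call STEP cost effective if incremental net monetary benefit (threshold × QALY difference − cost difference) is above zero, and report it with its confidence interval.
- Keep the ICER rule but apply it only when the QALY difference is positive. State the verdict for the two cases now left open: STEP costlier with fewer QALYs (dominated), and STEP cheaper with fewer QALYs.

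The first option is simpler, because one inequality covers all four combinations of cost and effect.

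For the threshold, give the SGD equivalents of both £20,000 and £30,000, with the exchange rate and its date, and report the verdict at each. If the two verdicts differ, the report should say so.

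The cost is a few sentences in the plan and standard analysis code. No new data, visits or participants are needed. The change should be made before the cost and QALY results are seen by arm.

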### Data monitoring

The Principal Investigator and Co-Investigators will be responsible for data and safety monitoring. The study coordinators will meet with the Principal Investigator fortnightly to provide recruitment updates and to review any adverse events or serious adverse events that occur during the study period. Due to the nature of the study procedures (i.e., screening interviews, questionnaire assessments, CBT interventions), there is not a high risk of adverse events or serious adverse events. In the case of such events, the Principal Investigator will be responsible for reporting any adverse events to the relevant authorities, regulatory bodies, and institutions as required.

## Discussion

The present study will evaluate the clinical, patient-centred, and economic effectiveness of a stepped-care intervention for ED patients with panic-related anxiety. We are aware of no prior studies seeking to evaluate screening and stepped-care for this patient population. In the short term, we expect that expedient care of patients presenting to the ED with panic attack symptoms will lead to improved clinical outcomes (i.e., symptom remission, improved quality of life) as well as reduced burden on the healthcare system due to reductions in unnecessary recurrent ED visits, investigations, and hospital admissions. In the long term, early identification and treatment of patients with panic-related anxiety may help to decrease waiting times at the ED and increase the availability of beds for patients needing urgent care. For example, a recent study from Taiwan found that psychiatric treatment of patients with panic disorder translated into a 30% reduction in related ED costs [27]. The two strategies being evaluated in the proposed RCT have the potential to significantly reduce healthcare costs while simultaneously improving patient outcomes.

## Study status

This trial commenced in June 2018. Baseline recruitment is still ongoing, with a planned end date of February 2023. Follow-up data collection will continue until February 2024.

## Data Availability

Not applicable.

## Abbreviations

*CBT*: Cognitive Behavioural Therapy
*CDR*: Clinical Decision Rule
*CGH*: Changi General Hospital
*CGI*: Clinical Global Impression Scale
*CONSORT*: Consolidated Standards of Reporting Trials
*CSPRS*: Collaborative Study Psychotherapy Rating Scale
*ED*: Emergency Department
*EQ-*5D: EuroQoL-5 Dimension
*ICER*: Incremental Cost-effectiveness Ratio
*ITT*: Intention-to-treat
*PDSS*: Panic Disorder Severity Scale
*PDSQ*: Psychiatric Diagnostic Screening Questionnaire
*QALYs*: Quality-adjusted Life Years
*RCT*: Randomized Controlled Trial
*SCID*: Structured Clinical Interview for DSM-5
*SF-*6D: Short Form Health Survey 6D
*SF-*12: 12-item Short Form Health Survey
*SGH*: Singapore General Hospital
*SKH*: Sengkang General Hospital
*VAS*: Visual Analog Scale
